## Rationale

Research shows that the prevalence of age-related functional disability in Brazil is large and still growing (Giacomin et al., 2018; Lima-Costa et al., 2022), but we do not know if this phenomenon is occurring in terms of IC. Recent research shows that IC is a valid measure for healthy aging in a country such as Brazil (Aliberti et al., 2022). A Latin American study showed that the reduction of IC in old age, including one or more of the factors in IC’s five domains, has a negative impact on the functional ability (FA) in the elderly (Prince et al., 2021). These associations must be reassessed with longitudinal studies in new environmental contexts such as the elderly population in Brazil (Martin and Ortuño, 2019).

Literature lacks studies with IC as the outcome variable, which is needed to indicate the normality values for different IC trajectories related to aging, with or without disability. Few studies have analyzed IC as a risk factor for compromising the FA of the elderly, measured by the degree of dependence in the performance of day-to-day activities, the risk of falls, and early mortality, while controlling for all possible known risks for functional losses—clinical, biological, genetic, and social (Prince et al., 2021). There are studies that point out that IC can predict the decline in activities of daily living (ADL) and instrumental activities of daily living (IADL) even after adjusting for sociodemographic factors and chronic diseases (Lu et al., 2021; Prince et al., 2021; Fong, 2019; Jonkman et al., 2018; Pan et al., 2021).

The key medical literature gaps that this proposed research aims to fill is how a set of comprehensive factors such as comorbidity, medications, biomarkers, pain, nutrition, strength, balance, gate, physical environment, hearing, vision, cognitive ability, motivation, and behavior, along with contextual factors such as demographic and socioeconomic factors, especially in Brazil, may work synergistically to impact ADL/IADL, falls, hospitalizations, and death as people age. The IC measure and its domains capture the complexity of the 14 factors’ interactions, allowing for the evaluation of the effect of not only each factor but also their joint effect.

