In addition, there is a pressing need in healthcare services for studies that assess the impact of effective health promotion strategies—cognitive stimulation, promotion of physical activity, and nutritional education—in preventing IC loss and maintaining FA in elderly people in Brazil. For this purpose, longitudinal observational studies are needed to initially assess these scientific assumptions and justify and guide future studies of controlled interventions.

This paper describes a proposal to 1) constitute a population cohort of elderly people living in a middle-class neighborhood in a large urban center in Brazil and 2) create a single indicator that expresses the trajectory of IC over the years. For this purpose, an assessment of the IC, the FA, and the social capital of the members at baseline and after 3 years will be carried out, establishing an average rate of IC decline, while controlling for the risk and protective factors—genetic, biological, clinical, behavioral, and environmental. The results will be vital for designing future interventional studies that prevent or mitigate functional ability losses associated with age. We intend, through the results from this cohort, to create an inclusive ecosystem of translational innovation in longevity integrated into a national/global innovation system in a continuous process of development and partnerships.

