**FIGURE 1 F1:**
[figure not shown]
Proposed study design.

In a period of 6 months, we expect that a team of trained interviewers will contact all potential cohort participants. Based on information from a recent study on the association of IC with the outcome incidence rates of functional dependence, falls, and death (Prince et al., 2021), we developed sample size estimates for comparing two proportions that represent the rates of outcomes in the groups that are exposed (low IC) and unexposed (medium or high IC) (see Tables 1, 2). Calculations considered various effect sizes (relative risk) and incidence or mortality rates. In estimating the sample size needed for this cohort study, this study considered the incidence of the expected outcome in the unexposed cohort (high IC), the risk assumed in the exposed group relative to the risk of the unexposed group (RR), a specific level of confidence (1-α = 0.95; where α = type I error rate), and a specific value of the desired sample power (1-β = 0.80; where β = type II error rate) for the detection of significant differences between the two cohorts. The outcome incidence rate in the cohort was used as a proxy for the expected outcome incidence rate in the unexposed group (high IC). The summary tables (Tables 1, 2 below) provide sample sizes for extremes of the assumed incidence and mortality rate values and the respective relative risks based on the confidence intervals of these measures. A total sample size of approximately 5,500 individuals (assuming 2,750 per group) will be sufficiently robust to maintain the desired power under most diverse scenarios and varying parameters, even if the dropout rate reaches approximately equal to 15% in the two cohorts. The exception will be with very small estimates of the relative risk of death (RR ≤ 1.3).

**TABLE 1 T1:** Sample sizes for specific values of functional loss (FL), incidence, and relative risk for intrinsic capacity (IC) and FL.

	Average risk ratio	Low risk ratio	High risk ratio
Risk ratios (RR)	1.91	1.7	3.0
Incidence rate among the unexposed group	0.0495	0.04925	0.04925
Confidence level (1-α)	0.95	0.95	0.95
Power (1-β)	0.8	0.8	0.8
Study type	Cohort	Cohort	Cohort
Sample per group (n_i_)	514	816	138
Total sample (n_1_+n_2_)	1,028	1,632	276

**TABLE 2 T2:** Sample sizes for specific values of total mortality (TM) and relative risk for IC and TM.

	Average risk ratio	Low risk ratio	High risk ratio
Risk ratios (RR)	1.66	1.3	2.0

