## Research questions and hypotheses to test

This proposed research will answer three scientific questions:1. Whether IC will decrease as expected at the 3-year follow-up (ICI at end-time ≤ ICI at baseline, or ∆IC < 0), regardless of the socioecological context, individual sociodemographic, behavioral, and clinical factors, and comorbidities (Charlson et al., 1987). This research will statistically test the hypothesis that ICI will not change over time (i.e., follow up IC = baseline IC, or ∆IC = 0).2. If DIC (or TIC) at baseline will be a strong predictor of FA, such as ADL (Mlinac and Feng, 2016), IADL (Hokoishi et al., 2001), falls (Kitcharanant et al., 2020), and death, regardless of the socioecological context, individual sociodemographic, behavioral, and clinical factors, and comorbidities (Charlson et al., 1987). That is, whether the proportion of these ADL/IADL losses, falls, and deaths will be greater in the decline group (e.g., DIC present) than in the unexposed group (e.g., DIC absent). Research will statistically test the hypothesis that there is no association between IC and ADL (or IADL) (e.g., relative risk for TIC or DIC and IADL = 1).3. Whether IC and its five domains are directly associated with a measure of QoL (i.e., World Health Organization Disability Assessment Schedule 2.0 (WHODAS 2.0)) (Prüss-Ustün et al., 2017) and LTPA (i.e., the International Physical Activity Questionnaire (IPAQ)) (Craig et al., 2003), regardless of the socioecological context, individual sociodemographic, behavioral, and clinical factors, and comorbidities (Charlson et al., 1987). Research will statistically test the hypothesis that there is no association between IC and either QoL or LTPA (e.g., relative risk for TIC or DIC and LTPA = 1).

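### Question 1 asks whether IC declines irrespective of a list of factors, but its stated test is one overall, unadjusted ∆IC = 0, which can support only an average change

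*Protocol article*

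**What the plan says.** All references are to the Protocol article.

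- **Research questions and hypotheses to test, question 1.** The question is whether IC decreases by the 3-year follow-up "regardless of the socioecological context, individual sociodemographic, behavioral, and clinical factors, and comorbidities". The test is then fixed: "This research will statistically test the hypothesis that ICI will not change over time", that is, ∆IC = 0. The same qualifying clause also appears in questions 2 and 3.
- **Rationale.** The aim is described as "establishing an average rate of IC decline, while controlling for the risk and protective factors". Studies with IC as the outcome are said to be "needed to indicate the normality values for different IC trajectories related to aging".
- **Study sample size and power calculation (text below Figure 1).** The confidence level is 0.95, and power is set separately as "a specific value of the desired sample power (1-β = 0.80; where β = type II error rate"). The size reads "A total sample size of approximately 5,500 individuals (assuming 2,750 per group") and is said to hold "even if the dropout rate reaches approximately equal to 15% in the two cohorts". It compares two proportions, which is question 2. No effect size, SD or power is given for ∆IC.
- **Explanatory variables: IC composite index.** The index runs from 0 (best) to 14 (worst). ∆IC is the last-wave value minus the baseline value.

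**The concern.** The question carries a qualifier about many factors, and the hypothesis carries none. A single test of the overall mean cannot tell a decline spread across the cohort from one concentrated in, say, one age band. In a cohort of this size the test will reject for a small mean change. If the result were then reported in the words of question 1, the conclusion would go further than the test. The Rationale also asks for values for different trajectories, and a pooled test does not supply them.

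**Working it through.** **The plan's own figure first.** Table 1, average risk ratio: p0 = 0.0495, p1 = 1.91 × 0.0495 = 0.0945, two-sided α = 0.05, power 0.80. With unpooled variance,

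n = (1.96 + 0.842)² × [p0(1 − p0) + p1(1 − p1)] / (p1 − p0)² = 514 per group,

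as stated (516 with pooled variance). The article does not state sidedness; two-sided reproduces this figure. The calculation does not concern question 1.

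**Number followed.**
- From the stated sample: 5,500 × 0.85 = 4,675.
- From the list of about 6,000 with 15% refusal, then 15% dropout: 6,000 × 0.85 = 5,100, and 5,100 × 0.85 = 4,335.
- Pessimistic: the earlier cohort in the Discussion lost 1,000 of 1,600 over 5 years (62.5%). Applied here, 5,500 × 0.375 gives about 2,062.

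**Power of the overall test.** z = mean × √n / SD, and power = Φ(z − 1.96). The SD of ∆IC is assumed. Take 20% worsening by 0.5 and 80% unchanged on average: mean = 0.2 × 0.5 = 0.10.

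| n | SD 1 | SD 1.5 | SD 2 |
|---|---|---|---|
| 4,335 | z 6.6, power >99% | z 4.4, power 99% | z 3.3, power 91% |
| 4,675 | >99% | >99% | 93% |
| 2,062 | >99% | 86% | 62% |

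At SD 3 and n = 4,675, power for the same mean is 63%.

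**A sharper case.** Let 25% worsen by 0.5 on average and 75% improve by 0.05: mean = 0.25 × 0.5 − 0.75 × 0.05 = 0.0875. At n = 4,675, power is 98% at SD 1.5 and 85% at SD 2, although three quarters of the cohort did not decline.

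**Smallest mean change with 80% power at n = 4,675.** 2.80 × SD / √4,675 = 0.041, 0.061, 0.082 and 0.123 points for SD 1, 1.5, 2 and 3. This equals 4% to 12% of people worsening by 1 point with the rest stable on average.

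**What else the article plans for change in IC.**
- *Objectives 3 and 5:* trajectories for the total cohort and for each segment. The segments are built partly from the IC index itself, so they are not levels of the listed factors.
- *Data analysis:* adjustment is called crucial, including for the evolution of IC, but no model is named for question 1.
- *Statistical models for IC as a predictor:* means or medians of ∆IC and the prevalence of decline, then IC by levels of ADL/IADL, falls and death. The ordinal regression of ∆IC is worded as a possibility. It has covariates and interactions, but its main X is IADL, falls or death, and the interactions are with that X.
- *Models for quality of life and leisure-time activity:* adjusted logistic models of decline, serving question 3.

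None estimates ∆IC by the listed baseline factors for question 1.

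**Sign.** With 0 best and 14 worst, worsening gives ∆IC > 0. Question 1 writes the expected decrease as ∆IC < 0. Elsewhere ∆IC is given a range of 0 to 10, which leaves no room for negative values.

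**The case against.** The strongest reply is that the clause means after adjustment. It recurs in questions 2 and 3, where the planned models are covariate-adjusted, and the Rationale speaks of controlling for factors. That is the more natural reading, and it takes much of the force from the minority-declines argument, since any test of a mean can reject in that situation. It does not close the gap, because the stated null is unadjusted. Adjustment alone would also change little: in a linear model, mean change standardized to the cohort largely returns the overall mean. The information lies in how change varies with the factors.

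A second reply is that the choice of model belongs to the fuller plan. This stands for modelling detail. It does not stand for the mismatch, because the article itself states both the question and its hypothesis.

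A third reply is that the magnitude rests on an assumed SD and split. It does, and with heavy attrition or a large SD the power falls well below 90%. The inferential point does not depend on it: a rejected overall null describes the mean only.

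A reader might go further and infer that the study will claim decline in every subgroup, or will deliver only one average. The article supports neither: the clause need not mean every stratum, and objective 5 plans results by segment.

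**Conclusion.** The point holds as a mismatch between question 1 and its only stated hypothesis. Rejecting ∆IC = 0 would support an average change in the cohort and no statement about the listed factors, on either reading of the clause. At 4,335 to 4,675 followed, a mean change of 0.10 points is detected with power of about 91% or more for an assumed SD of 1 to 2, wherever in the cohort that change sits. It is not an absence of all adjusted or stratified work on IC change; what is missing is an analysis of that kind tied to question 1. The contradictory sign of decline is a separate, plain error in the same question.

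**What to change.** 1. Settle the sign first: either reverse the index or state that decline means ∆IC > 0, and correct the stated range of ∆IC.
2. For question 1, regress ∆ICI on a short prespecified list of baseline factors, such as age band, sex, and socioeconomic, behavioural and clinical factors.
3. Report mean change with a confidence interval at each level, with tests of whether change differs by factor.
4. State the conclusion from the overall test as an average decline only. Base any wording on consistency on the size and direction of the stratum estimates and the heterogeneity results.

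Do not require every stratum interval to exclude zero. In a 10% stratum of 4,335 to 4,675 people at an assumed SD of 1.5, SE = 1.5/√434 to 1.5/√468, about 0.07. Under a truly uniform change of 0.10, power per stratum is then Φ(0.10/SE − 1.96), about 28% to 30%, so such a rule would usually fail even when decline is uniform.

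The cost is revised wording and one model on data already planned for collection. The downside is the lower precision of the stratum estimates.

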Second, the change in the ICI value during the follow-up time in the cohort will be measured and referred to as “ICI delta” (∆IC). The ∆IC is calculated as the difference between the ICI measured in the last follow-up wave minus the ICI measure at the baseline (variable with values between 0 and 10). Third, we will consider the presence of a decline in IC (DIC) if one or more declines in an IC domain are found from the baseline measure. As an example of IC domain decline in the cognitive dimension, a Montreal Cognitive Assessment (MoCA) score of 22 at follow-up versus 27.0 at baseline is considered a decline and probable “dementia” (Nasreddine et al., 2005). The opposite will be classified as no decline.

Finally, a weighted measure of IC (WIC) will be derived from the multivariate regression result of the association between IC subdomains and IADL loss, which will be adjusted for individual sociodemographic factors (see the Analysis section below for detailed description of WIC).

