#### Statistical models to assess whether IC is a predictor of ADLs/IADLs, falls, and death

Two Cox regression models will be evaluated to estimate the incidence rates of outcomes (i.e., functional loss measured by IADLs, falls, and death) associated with IC at baseline (e.g., TIC, DIC, and WIC) (ElHafeez et al., 2021). Cox’s first model has the indicator variable X to denote the association with each of the two groups of IC exposure at baseline (e.g., X1 = 1 for medium and high TIC and X1 = 0 for low TIC), with Y being the adverse incident at 3 years of follow-up (loss of ADLs/IADLs, falls, and death); survival times will be measured by the interval from the first assessment to the adverse incident. For subjects who do not experience an adverse incident, the follow-up time will be the last evaluation of the study.

The model also comprises a collection of covariates V with the potential to be a confounding factor in the association between Y and X (e.g., sociodemographic factors), and W would be the potentially interactive term between X and V (e.g., sex * TIC). The regression coefficient of X describes the effect of TIC on outcome Y, that is, the risk of greater or lesser loss of ADL/IADL, falls, and death for those exposed to medium or high TIC relative to those exposed to low TIC. The W terms will assess whether there is a positive interaction between TIC and one of the V confounders that have been identified to be potentially interacting. The model will extend by substituting TIC for DIC or WIC as the main exposure variable X. Alternatively, we can also model Y (e.g., IADL) as a function of X (either TIC, DIC, or WIC) and the same set of V and W using logistic regression to estimate the odds ratio of the outcomes.

We will evaluate the IC trajectory through changes in IC scores (∆IC or WIC) or the presence of IC decline (DIC) after 3 years, along with their associations with IADL outcomes, falls, and death. For example, the mean/median of ∆IC (or WIC) and the prevalence of DIC will be generated at baseline and at the end of the 3-year follow-up. We will then generate the mean/median or prevalence of IC measure by levels of ADL/IADL, falls, and death. The means/medians of IADLs and the incidence of falls and death after 3 years of follow-up will also be estimated.

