In contrast, we should also be able to model Y as ∆IC (ordinal variable with values from 0 to 10) as a function of a main vector X (IADL, falls, or death) and a collection of parameters V and W similar to the previous model, but using a multivariate ordinal regression model with a latent variable specification, where composite probability methods are applied to estimate model parameters (Hirk et al., 2019).

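### IC decline (DIC) exists only once a follow-up assessment is made, yet it is used as a baseline exposure for death, falls and ADL/IADL loss, and delta IC is modelled on death

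*Protocol article*

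**What the plan says.** **Definitions.** The section on the IC composite index classes DIC as present "if one or more declines in an IC domain are found from the baseline measure". Its example is a MoCA "score of 22 at follow-up versus 27.0 at baseline is considered a decline". Delta IC is "the difference between the ICI measured in the last follow-up wave minus the ICI measure at the baseline". The Rationale says that the assessment of IC, functional ability and social capital "at baseline and after 3 years will be carried out".

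**Use.** Research question 2 asks "If DIC (or TIC) at baseline will be a strong predictor of FA" and compares ADL/IADL losses, falls and deaths between people with and without DIC. The section on models for ADLs/IADLs, falls and death describes Cox models for outcomes "associated with IC at baseline (e.g., TIC, DIC, and WIC"), with survival time counted from the first assessment. It then puts DIC in place of TIC as the main exposure. The same section states that "the prevalence of DIC will be generated at baseline and at the end of the 3-year follow-up". Finally, it proposes an ordinal model for delta IC "as a function of a main vector X (IADL, falls, or death").

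**The concern.** A Cox model timed from baseline needs an exposure known at baseline, or one that is allowed to change over time. DIC is neither as the plan uses it. Three consequences follow.

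- **Death.** Only survivors to reassessment can be classed as declined. Their time from baseline to that visit is immortal, and counting it as exposed time makes decline look protective.
- **ADL/IADL loss and falls.** DIC does exist in reassessed survivors, but it is read at or after the time when the outcome may have occurred. The temporal order that the Discussion claims as a strength of the design is then lost for these analyses.
- **Delta IC on death.** People who die before reassessment have no last-wave ICI, so the dependent variable does not exist for those who supply the deaths.

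At stake is whether the DIC part of question 2 measures prediction or an artefact of who lived long enough to be classified.

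**Working it through.** **1. The plan's mortality figure and what it was built for.** Table 2 gives mortality of 0.04826 among the unexposed and 926 per group at RR 1.66. With two-sided alpha 0.05 (sidedness assumed), power 0.80 and p1 = 1.66 × 0.04826 = 0.08011:

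n = (1.960 + 0.842)² × [p0(1−p0) + p1(1−p1)] / (p1−p0)² = 925.5, rounded up to 926 per group.

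This reproduces the stated figure. The groups behind it are low versus medium or high IC at baseline, not DIC.

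**2. Deaths expected in 5,500.** The protocol does not say whether 0.04826 is a 3-year risk or an annual rate, so both are shown.

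| | 3-year risk | Annual rate, constant hazard |
|---|---|---|
| Unexposed figure applied to everyone | 5,500 × 0.04826 = 265 | 5,500 × (1 − e^(−3×0.04826)) = 741 |
| 2,750 per group, RR 1.3 | 2,750 × 0.04826 × 2.3 = 305 | 842 |
| 2,750 per group, RR 2.0 | 2,750 × 0.04826 × 3.0 = 398 | 1,062 |

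The lower annual-rate entries are 2,750 × [(1 − e^(−3×0.04826)) + (1 − e^(−3×0.04826×RR))].

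**3. If IC is reassessed only at 3 years.** None of these deaths has a DIC or delta IC value. Leaving the dead out gives 0 deaths in both DIC groups, so no relative risk can be computed. Coding them as not declined, with an assumed 30% decline among survivors and no true association, gives:

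- 3-year risk: 0/1,570 declined versus 265/3,930 not declined.
- Annual rate: 0/1,428 versus 741/4,072.

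The relative risk is 0 by construction in both cases.

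**4. If there is an interim wave.** As an illustration, assume one reassessment at 18 months that fixes DIC, 30% decline among those alive then, constant hazard, no true association, and early deaths coded as not declined. On the 3-year-risk reading, the risk per half is 1 − √(1 − 0.04826) = 0.02443.

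- Early deaths: 5,500 × 0.02443 = 134. Alive at 18 months: 5,366. Declined: 0.30 × 5,366 = 1,610.
- Later deaths in the declined: 1,610 × 0.02443 = 39, a risk of 0.0244.
- Not declined: 5,500 − 1,610 = 3,890, with 265 − 39 = 226 deaths, a risk of 0.0581.
- Apparent RR = 0.0244 / 0.0581 = 0.42, where the truth is 1.

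The same steps with 50% declining, and with the annual-rate reading, give 0.34 to 0.44. Dropping the early deaths removes this distortion with a single interim wave, because the analysis is then in effect a landmark analysis. With several waves, people who live longer still have more chances to be classed as declined.

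**5. Time order for the other outcomes.** With a single 3-year reassessment, DIC and loss of ADL/IADL are read at the same visit. Falls are recorded for the preceding year, that is, before the visit that defines DIC.

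**The case against.** **The schedule is not settled.** The Rationale points to baseline and 3 years, but delta IC is defined by the last follow-up wave, the Discussion refers to scheduled evaluations, and the design figure is not shown. This stands. A reader might infer that no one classed as declined can die in the study and that the hazard ratio must be 0. That holds only under a single 3-year reassessment. With interim waves the fault is an exposure that changes over time and is treated as fixed at baseline.

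**The main contrast is sound.** The first Cox model uses baseline TIC, and the sample size rests on baseline IC level. DIC enters as a substitution, and the delta IC model is worded tentatively. This also stands: death remains answerable through TIC. It does not rescue DIC, which question 2 itself names.

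**A descriptive framing is already present.** The models section also presents DIC after 3 years alongside its associations with outcomes. That wording is acceptable, but it sits beside the baseline-exposure wording and does not replace it.

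**Imputation after death.** A reader might infer that the multiple-imputation rule would fill in IC for the dead. The documents do not say so. The rule is generic and does not mention deaths, and deaths at the unexposed figure alone are 265/5,500 = 4.8%, below its 5% trigger. Dropout, which the plan puts at up to about 15%, or the plan's relative risks (305/5,500 = 5.5% at RR 1.3) would pass it. This supports one clarifying sentence, not a charge of error.

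**Conclusion.** The concern holds in limited form. By the plan's own definitions DIC and delta IC do not exist at baseline, and the hypothesis, the Cox exposure and the planned baseline prevalence all contradict that. Modelling delta IC on death has no dependent variable for people who die before reassessment. This is an error in what is stated, not detail left to an analysis plan.

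Its size depends on the schedule. With reassessment only at 3 years, the 265 to 1,062 deaths expected across the readings above carry no DIC, and the relative risk for death is undefined or 0. With an interim wave, a true null could appear as an RR of about 0.34 to 0.44 if early deaths are coded as not declined. These figures rest on both readings of 0.04826, constant hazard, and assumed decline of 30% to 50%.

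The documents do not support the wider inference that question 2 as a whole fails. Baseline TIC and the stated sample size are untouched.

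**What to change.** 1. In research question 2 and the Cox section, use baseline TIC as the exposure for incident ADL/IADL loss, falls and death. WIC may be used if scored from baseline items only. Because its weights come from regression on IADL loss, use it for that outcome only with weights derived or validated on separate data.
2. Delete DIC at baseline as an exposure, and delete its baseline prevalence.
3. State the IC assessment schedule. Relate DIC or delta IC only to events after the visit that defines them, with the clock started at that visit (landmark). If no follow-up comes after that visit, report the association as concurrent.
4. Remove death from the explanatory vector of the delta IC model. Showing decline or death as a composite beside delta IC in survivors is optional.
5. Add one sentence saying that the multiple-imputation rule does not apply to IC values after death.

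**Cost.** Wording only, since the article says no data have been collected. The downside is small: within the 3-year study the DIC–death question is either dropped or confined to deaths after a landmark visit.
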